## Abstract

**Background:**

Cognitive frailty (CF), characterized by the coexistence of mild cognitive impairment and physical frailty in the absence of dementia or other neurodegenerative diseases, is a significant risk factor for dementia and functional decline in older adults. Although Du-moxibustion has shown potential benefits in improving CF, the effect of spine-pinching therapy remains underexplored.

**Objective:**

This study aims to evaluate, for the first time, the efficacy and safety of Du-moxibustion combined with spine-pinching therapy in older adults with prefrailty and CF.

**Methods:**

This is a prospective, single-center, randomized, single-blind, 4-arm parallel controlled trial. A total of 156 older adults with prefrailty and CF will be recruited and randomly assigned to 1 of 4 groups: routine care group, Du-moxibustion group, spine-pinching group, or combined intervention group. The intervention will last for 8 weeks. The primary outcome is the change in Montreal Cognitive Assessment score. Secondary outcomes include the Fried frailty phenotype, Barthel Index (activities of daily living), 15-item Geriatric Depression Scale, 36-item Short Form Health Survey, global frailty status, and traditional Chinese medicine syndrome scores. Outcome assessments will be performed at baseline (wk 0), midintervention (wk 6), postintervention (wk 8), and follow-up (wk 12).

**Results:**

Recruitment for this study is scheduled to commence in March 2026 and will end in June 2027 (recruitment and intervention). All follow-up and data collection activities will be finalized by October 2027. Results are anticipated to be completed in the first quarter of 2028.

**Conclusions:**

This study is expected to provide high-quality evidence for the clinical efficacy of Du-moxibustion combined with spine-pinching therapy in managing CF and contribute to the integration of traditional Chinese medicine external therapies in the promotion of healthy aging. Although the single-blind design may introduce expectancy bias, strict randomization procedures and standardized interventions will enhance the reliability and scientific rigor of the results.

## Introduction

Cognitive frailty (CF), defined as the coexistence of physical frailty and mild cognitive impairment (MCI) in the absence of dementia, has been increasingly recognized as a critical geriatric syndrome associated with accelerated functional decline, disability, hospitalization, and mortality [1]. Recent epidemiological studies report that the prevalence of CF ranges from 1% to 12% in community-dwelling older adults and is substantially higher among hospitalized populations [2]. With the rapid demographic shift in China, the number of older adults is projected to exceed 280 million by 2030, suggesting that the burden of CF will continue to rise [3].

Prefrailty, a transitional and potentially reversible stage within the frailty continuum, affects more than half of older adults and represents an important window for targeted preventive intervention [4,5]. However, evidence indicates that prefrailty is frequently underrecognized and undertreated in clinical settings, resulting in missed opportunities to delay or reverse progression toward frailty and cognitive decline [6,7]. Current Western medicine approaches for managing CF—including pharmacological treatments such as cholinesterase inhibitors and nonpharmacological strategies such as cognitive training, physical exercise, and psychosocial support—offer limited benefits on combined cognitive and physical outcomes, and pharmacological approaches often carry risks of adverse events in older adults [8,9]. These limitations highlight the need for safe, multidimensional, and holistic interventions specifically tailored to the population with prefrailty.

Traditional Chinese medicine (TCM) emphasizes individualized, syndrome-based treatment and has shown potential in improving both cognitive performance and frailty-related physical deficits. External TCM therapies such as Du-moxibustion and spine-pinching (niefu) therapy are believed, according to TCM theory, to regulate physiological balance, support spleen-kidney function, and enhance vitality. Emerging evidence suggests that Du-moxibustion may improve cognitive function, physical frailty symptoms, gait performance, and inflammatory biomarkers in older adults with frailty or cognitive impairment [10-12]. Spine-pinching therapy, widely used in TCM rehabilitation to modulate meridian pathways and autonomic function, has demonstrated preliminary benefits in improving gastrointestinal function, physical vitality, and neurocognitive-related symptoms [13,14]. Nevertheless, despite their complementary theoretical basis, no randomized controlled trial (RCT) has evaluated the combined effects of Du-moxibustion and spine-pinching therapy in older adults with prefrailty-related CF.

To address this gap, this study will conduct an RCT to evaluate the efficacy and safety of Du-moxibustion combined with spine-pinching therapy in older adults diagnosed with prefrailty and CF, based on both Western diagnostic criteria and a specific TCM syndrome pattern (“spleen–kidney deficiency with Du meridian obstruction”). This trial aims to provide high-quality evidence supporting an integrative, multidimensional intervention strategy for improving cognition, frailty status, emotional well-being, and quality of life in this growing vulnerable population.

## Methods

### Ethical Considerations

This study has been approved by the ethics committee of Hangzhou First People’s Hospital (approval 2025ZN211-1), in compliance with the Declaration of Helsinki (Edinburgh 2000 Amendment) and medical ethical requirements. Concurrently, this trial is registered with the International Traditional Medicine Clinical Trial Registry under the registration number ITMCTR2025001589. Participants received comprehensive study information, including the study’s purpose, potential risks (eg, burns or emotional distress), benefits, and their right to withdraw at any time, and provided written informed consent prior to screening. Serious adverse events will be reported to the ethics committee within 24 hours and monitored by the Data and Safety Monitoring Committee (DSMC) throughout the 8-week intervention and 12-week follow-up. Patients or their legal representatives were informed in an accessible language about the study objectives, methods, and procedures. During the preparation of this study, generative artificial intelligence tools were used to assist with translation and linguistic refinement. Results will be submitted to peer-reviewed SCI (Science Citation Index) journals and presented at conferences on geriatrics, TCM, and nursing. Anonymized data will be uploaded to an open-access repository for validation and future research.

### Study Design

This study is designed as a prospective, single-center, randomized, single-blind, 4-armed parallel controlled clinical trial. A total of 160 eligible patients will be randomly assigned in a 1:1:1:1 ratio to one of four groups via a centralized randomization system: routine care group, Du-moxibustion group, spine-pinching group, and combined intervention group (Du-moxibustion+spine-pinching). The intervention will last for 8 weeks. The routine care group will receive health education once per week, while the other 3 groups will receive treatment twice per week: Du-moxibustion (30 min/session), spine-pinching (15‐20 min/session), and combined therapy (45‐50 min/session). Outcomes will be assessed at baseline, midintervention, postintervention, and follow-up.

### Participants

#### Source of Participants

Participants will be recruited from the geriatrics and neurology outpatient clinics of Hangzhou First People’s Hospital between March 2026 and June 2027. Recruitment will be conducted through outpatient screening and community-based advertisements.

#### Inclusion Criteria

Participants must meet all of the inclusion criteria summarized in Textbox 1.

Textbox 1.Inclusion criteriaAged ≥60 yearsFried frailty phenotype score between 1 and 2, indicating a prefrail stateDiagnosed with cognitive frailty, as indicated by a Montreal Cognitive Assessment score of <26Diagnosed with the traditional Chinese medicine (TCM) syndrome of “spleen-kidney deficiency with Du meridian obstruction,” according to the Standards for TCM Disease and Syndrome Diagnosis and Efficacy Evaluation [15] (see “Diagnostic Criteria for CF” section for diagnostic criteria: ≥2 primary symptoms, ≥2 secondary symptoms, and corresponding tongue and pulse signs)Able and willing to provide written informed consent and comply with the study protocol

#### Diagnostic Criteria for CF

Participants will be screened based on both Western medicine and TCM diagnostic criteria.

##### Western Medicine Diagnostic Criteria

Based on the definition by the International Academy on Nutrition and Aging or the International Association of Gerontology and Geriatrics [1], the diagnostic criteria for CF include: (1) patient or family member reports subjective cognitive decline; (2) no diagnosis of dementia, with a Clinical Dementia Rating score of 0.5; and (3) Mini–Mental State Examination score ≤27 or MoCA score <26.

These criteria align with the international consensus definition of CF—coexistence of physical frailty and MCI without dementia.

##### TCM Diagnostic Criteria

According to the Standards for TCM Disease and Syndrome Diagnosis and Efficacy Evaluation [15], patients must meet the following criteria for the TCM syndrome of “spleen-kidney deficiency with Du meridian obstruction”:

Primary symptoms: fatigue, soreness, and weakness of the waist and knees, poor appetite, and insomnia;Secondary symptoms: dizziness, abdominal distension, lower back pain, abdominal cold pain, tinnitus, edema, pale or flushed complexion, aversion to cold or 5-center heat, spontaneous or night sweating, dry mouth or thirst, frequent urination or nocturia, and loose or dry stools;Tongue and pulse signs: pale or swollen tongue, or red tongue with scant coating; weak, deep-slow, or thin-rapid pulse.

A diagnosis can be made when the patient presents with at least 2 primary symptoms, 2 secondary symptoms, and characteristic tongue and pulse signs.

### Exclusion Criteria

Participants will be excluded if they meet any of the criteria summarized in Textbox 2.

Textbox 2.Exclusion criteriaDiagnosed with Alzheimer disease or other forms of dementiaSuffering from severe cardiovascular, cerebrovascular, hepatic, renal, or psychiatric disordersReceived Du-moxibustion, spine-pinching, or other external traditional Chinese medicine therapies in the past 6 monthsAllergic to moxa, ginger, or other topical substances used in the intervention, or have skin ulcers, infections, or other conditions that contraindicate treatmentUnable to maintain prone or lateral positions due to severe spinal deformities, arthritis, or other conditionsParticipated in other exercise, cognitive training, or intervention studies within the past 3 months

### Criteria for Withdrawal or Discontinuation

Participants will be withdrawn or excluded from analysis under the following circumstances: (1) voluntary withdrawal or loss to follow-up before completing the intervention, (2) serious adverse events or complications during the study, (3) poor compliance leading to discontinuation of treatment, and (4) development of severe illness during the study period that requires termination of participation.

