### Intervention Adherence Management

A dedicated team member will record the execution of interventions and patient feedback. Prior to each session, the research nurse will inform, supervise, and reassure the participants. If a participant misses 2 consecutive sessions or completes less than 80% of the interventions, the reasons will be analyzed, and a decision will be made regarding their inclusion in the final analysis.

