### Statistical Analysis

#### Overview

Data analysis will be conducted using SPSS (version 27.0; IBM Corp). The primary analysis will be based on the intention-to-treat principle, supplemented by per-protocol analysis. Missing data will be imputed using the last observation carried forward method. Results will be expressed as mean (SD) or median (IQR), as appropriate.

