#### Primary Outcome Analysis

Analysis of the sole primary outcome is focused on the difference in MoCA scores at week 8 between the combined intervention group and the routine care group. We will use ANCOVA for this comparison, adjusting for the baseline MoCA score as a covariate, to derive the primary efficacy conclusion (significance level set at *P*<.05).

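### Exclusions from analysis after withdrawal, adverse events or poor adherence are not confined to the per-protocol set and conflict with the intention-to-treat primary analysis

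*Protocol article*

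**What the plan says.** Three sections of the protocol article bear on who is analysed.

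- **Statistical Analysis, Overview.** "The primary analysis will be based on the intention-to-treat principle, supplemented by per-protocol analysis." The same paragraph adds: "Missing data will be imputed using the last observation carried forward method."
- **Criteria for Withdrawal or Discontinuation.** "Participants will be withdrawn or excluded from analysis under the following circumstances". The four triggers are "voluntary withdrawal or loss to follow-up before completing the intervention"; "serious adverse events or complications during the study"; "poor compliance leading to discontinuation of treatment"; and severe illness that requires participation to end.
- **Intervention Adherence Management.** For a participant who misses 2 consecutive sessions or completes under 80% of the intervention, the reasons are reviewed and "a decision will be made regarding their inclusion in the final analysis".

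The affected comparison is the sole primary one: week 8 MoCA, combined intervention against routine care. Primary Outcome Analysis says: "We will use ANCOVA for this comparison, adjusting for the baseline MoCA score as a covariate". The section on multiple comparisons reserves formal inference for this comparison.

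**The concern.** An intention-to-treat analysis keeps every randomized participant in the assigned group, whatever happens afterwards. All the listed triggers, and the adherence rule, are events after randomization. Neither section says that its exclusions apply only to the supplementary per-protocol analysis. One team could follow the withdrawal section and drop these participants from the primary comparison. Another could follow the statistical section and keep them. The two could report different primary results, each with support in the protocol.

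At stake is the protection that randomization gives to the only confirmatory comparison. Some triggers can plausibly act unequally across arms. Safety Monitoring lists burns and moxibustion syncope as events of the intervention groups, and emotional discomfort as the event to watch for in the control group. A combined session lasts 45 to 50 minutes, against 30 minutes of education in routine care. The adherence decision has no stated criteria or decision-maker, and the section does not require it to be made blind to group.

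**Working it through.** **1. The passages side by side**

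| Question | Statistical Analysis, Overview | Withdrawal criteria and adherence section |
|---|---|---|
| Does a participant who stops early stay in the primary analysis? | Yes, under intention-to-treat | May be excluded from analysis |
| Does a participant with under 80% attendance stay in? | Yes | Decided case by case |
| Which analysis set is meant? | Intention-to-treat primary, per-protocol supplementary | None named |
| What happens to missing values? | Last observation carried forward | Not addressed |

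Carrying values forward serves a purpose only if participants with missing data are kept. It therefore supports the intention-to-treat reading, but no text reconciles the two columns.

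**2. The plan's own figure for losses**

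Sample Size Calculation gives 33 effective participants per group and 15% dropout: 33/(1 − 0.15) = 38.82, rounded up to 39, and 4 × 39 = 156. This reproduces. About 0.15 × 39 = 5.85, or 6 per arm, could be subject to the conflicting rules if losses run as planned.

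**3. Can the adherence rule act unequally?**

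Study Design and Quality Control give routine care one session a week (8 in total). The Routine Care Group section and Table 1 give two a week (16 in total). The active arms have 16.

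- With 8 sessions, missing 2 leaves 6/8 = 75%, below 80%.
- With 16 sessions, missing 3 leaves 13/16 = 81%, and missing 4 leaves 12/16 = 75%.

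On one of the two stated schedules, the same 80% rule is reached after 2 missed sessions in routine care and after 4 in the active arms. The schedule statements need to be reconciled. Here they show only that the rule need not act alike across arms.

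**4. Illustration A: exclusion in one arm only, no true effect**

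Inputs: SD 4, 39 randomized per arm and 15% excluded (Sample Size Calculation). Assumptions of this review: exclusion in one arm only, correlation 0.3 to 0.5 between exclusion tendency and outcome, two-sided 5% test, normal approximation without covariate adjustment.

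- Removing the lowest 15% outright raises an arm's mean by SD × φ(z₀.₁₅)/0.85 = 4 × 0.233/0.85 = 4 × 0.274 = 1.10 points.
- With correlation 0.3 the shift is 0.3 × 1.10 = 0.33. With 0.5 it is 0.5 × 1.10 = 0.55.
- SE = 4 × √(1/33 + 1/39) = 0.946.
- Type I error = 1 − Φ(1.96 − shift/SE) + Φ(−1.96 − shift/SE), which is 6.4% for 0.33 and 8.9% for 0.55.

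**5. Illustration B: exclusion in both arms, no true effect**

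Assume that excluded participants score d = 2 to 4 points below those kept. The bias is then (difference in exclusion proportions) × d, with SE computed from 39 × (1 − proportion excluded) in each arm.

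| Excluded, combined vs routine care | Bias (points) | Type I error |
|---|---|---|
| 15% vs 15% | 0 | 5.0% |
| 20% vs 10% | 0.2 to 0.4 | 5.5% to 6.9% |
| 25% vs 5% | 0.4 to 0.8 | 6.9% to 12.8% |

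Swapping the arms reverses the sign of the bias.

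**The case against.** The best defence is that the statistical section already states the right principle and should govern. The withdrawal sentence offers withdrawal as an alternative to exclusion, under a heading about withdrawal and discontinuation. A per-protocol set needs exclusion rules, and these two sections may have been meant to supply them. That intent is plausible, but the text does not state it, and the adherence section speaks of the final analysis without naming a set. Because the article states incompatible rules, the point does not depend on detail that a separate analysis plan might hold.

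It is also fair that dropout is planned at 15% in every group, that equal and equally selective exclusion causes no bias, and that routine care could lose more participants than the active arms. All of this stands, and it limits what can be said about size and direction. The Blinding section keeps data analysts blind and places final unblinding after the analysis. That helps, but it does not say who takes the adherence decision, and the practitioners are not blind.

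Three stronger readings are tempting and are not supported:

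- **Participants with serious adverse events vanish from the safety evaluation.** Safety Monitoring records events after each session, requires serious events to be reported to the ethics committee within 24 hours, and gives the monitoring committee oversight through follow-up. At most, it is unclear whether the exclusion wording reaches the safety summaries.
- **Hardly anyone is left for imputation.** The triggers are qualified: loss must precede completion of the intervention, poor compliance must lead to discontinuation, and illness must require participation to end. Someone who completes treatment and then misses a visit is not excluded by the first trigger.
- **The effect would be overstated by 18%.** This comes from 0.85 × 3 = 2.55 against 3.0. It assumes that everyone removed from the combined arm gains nothing over routine care, and it compares an effect in all randomized participants with an effect in completers. The documents do not support that assumption.

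**Conclusion.** The point holds as a conflict in the text: two sections permit exclusions after randomization without confining them to the per-protocol set, while the statistical section makes intention-to-treat primary. This conclusion rests on no number.

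The consequence is conditional. Exclusion can bias the combined versus routine care comparison when it is related to outcome and differs by arm. The calculations are illustrations under the stated assumptions: shifts of 0.33 to 0.55 points and type I error of about 6% to 9% with one-arm exclusion, and none with equal and equally selective exclusion. A reader might conclude that the primary analysis is already a completers analysis. The documents show only that it could become one if the exclusion wording is followed. Because the sole confirmatory comparison is affected and the remedy is cheap, the text should be corrected before enrolment proceeds.

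**What to change.** 1. **Criteria for Withdrawal or Discontinuation.** Delete the words that allow exclusion from analysis. State that meeting these criteria does not remove a participant from the primary analysis, which includes all randomized participants in their assigned groups.
2. **Follow-up.** State that week 6, 8 and 12 outcomes will still be collected after treatment stops from those who agree, and that these participants stay in the safety summaries.
3. **Intervention Adherence Management.** Restrict the criteria of 2 consecutive missed sessions and 80% completion to the supplementary per-protocol set, with membership decided blind to group.
4. **Clinical rules.** This change concerns only who is analysed and leaves the rules for pausing or stopping treatment as they are. The sponsor should reconcile the withdrawal criteria with the Du-Moxibustion Group, Combined Intervention Group and Safety Monitoring sections, which provide for suspending, pausing or terminating the intervention.

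The cost is wording in two sections and some effort to follow participants who stop treatment. The planned 39 per group and 156 in total do not change. Outcomes not collected after treatment stops cannot be recovered later, so the change should be made early.

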### Du-Moxibustion Group

Details pertaining to the participants in the Du-moxibustion group are as follows:

Treatment site: this implies the Du meridian line, from Dazhui (GV14) to Yaoshu (GV2), covering thoracic vertebrae T1 to lumbar vertebrae L5, as illustrated in Figure 1.Materials: these include a herbal powder (equal parts of astragalus, codonopsis, chuanxiong, and carthamus), fresh ginger paste (thickness: 1.5 cm), mulberry paper, moxa cones (1.5 cm diameter, approximately 2 g each), alcohol swabs, and an ignition device.Procedure: these include (1) the participant lying in the prone position; (2) the back is cleaned and dried; (3) the herbal powder is applied along the Du meridian, covered with mulberry paper; (4) a 1.5 centimeter layer of ginger paste is spread over the area; (5) Moxa cones are placed in shallow depressions formed in the ginger layer; (6) the cones are ignited and burned for approximately 30 minutes, and (7) the residues are cleaned and the skin is inspected for irritation or burns.Environment: the treatment room must be well-ventilated and equipped with smoke evacuation systems.Frequency and duration: the frequency is twice per week for 8 consecutive weeks (total of 16 sessions). The session duration of Du-moxibustion was set at 30 minutes based on previous clinical trials, in which moxibustion treatments typically lasted 20 to 30 minutes, ensuring both sufficient stimulation and patient safety [16].Safety monitoring: skin reactions (eg, redness and burns) will be observed after each session. Cold compresses or suspension of treatment will be applied if necessary. All findings will be recorded in the CRF.

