### Spine-Pinching Group

Details pertaining to the participants in the spine-pinching group are as follows:

Position: the position should be prone, with the back exposed.Method: starting from the sacrococcygeal region along the midline of the spine, pinch the skin and move upward toward the seventh cervical vertebra. The procedure is performed along 3 lines centered on the spine (left bladder meridian, right bladder meridian, and Du meridian). For each line, perform 3 pinches, followed by lifting (pinch 3 times and lift once) for 4 to 5 cycles. Acupressure is applied to the Xinshu (HT7), Shenshu (KI3), Pishu (SP3), Weishu (ST25), Ganshu (LV3), and Sanjiaoshu (SJ5) points (1 min per acupoint). The acupoint locations are shown in Figure 2, and the manipulation technique is illustrated in Figure 3. The total treatment duration is 15 to 20 minutes.Frequency and duration: the frequency is twice per week for 8 weeks, totaling 16 sessions.Safety: after each intervention, skin tenderness or muscle discomfort will be monitored and recorded in the CRF.

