### Combined Intervention Group

Details pertaining to the participants in the combined intervention group are as follows:

Intervention order: following the “first unblock, then replenish” principle, spine-pinching therapy is performed first (to unblock meridians and regulate qi and blood), followed by Du-moxibustion (to warm and regulate the Du meridian and tonify the kidney and marrow).Procedure: the spine-pinching procedure is the same as described in the “Spine-Pinching Group” section, and the Du-moxibustion procedure is the same as described in the “Du-Moxibustion Group” section. The total treatment time is 45 to 50 minutes.Environment: the treatment room should have proper ventilation and be equipped with smoke-extraction devices.Frequency and duration: the frequency is twice per week for 8 weeks, totaling 16 sessions.Safety: after each intervention, skin redness, burns, or tenderness will be monitored. If necessary, cold compresses or suspension of treatment will be applied, and the results will be recorded in the CRF.

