### Safety Monitoring

Adverse events will be monitored and recorded after each intervention session, including moxibustion burns, skin allergies, moxibustion syncope, and localized tenderness in the intervention groups, as well as psychological or emotional discomfort (eg, anxiety) in the control group. Adverse events will be classified by severity: mild (no treatment required), moderate (intervention paused; eg, cold compress for burns), and severe (intervention terminated and referral required; eg, hospitalization). The research nurse will document the time, symptoms, management, and outcomes in the CRF. Serious adverse events, such as hospitalization or life-threatening conditions, will be reported to the ethics committee within 24 hours. The DSMC will oversee trial safety and may trigger unblinding if necessary. Monitoring will cover the 8-week intervention and 12-week follow-up periods.

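### Withdrawal item (2) ties an ungraded safety event to leaving the study or the analysis, at odds with the graded safety scheme and the intention-to-treat analysis, and mainly affecting the active arms

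*Protocol article*

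**What the plan says.** **Criteria for Withdrawal or Discontinuation.** The list opens with "Participants will be withdrawn or excluded from analysis under the following circumstances". Its second item is "2) serious adverse events or complications during the study". The item does not define or grade complications.

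**Safety Monitoring.** Adverse events are graded in three tiers. The lower two are "mild (no treatment required), moderate (intervention paused; eg, cold compress for burns"). The third is "severe (intervention terminated and referral required; eg, hospitalization"). Only this third tier ends the intervention, and the section does not say that the participant then leaves the study or the analysis. It lists moxibustion burns, allergic skin reactions, syncope and local tenderness for the intervention groups, and psychological or emotional discomfort for the control group.

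**Arm descriptions.** For skin reactions, the Du-Moxibustion Group section says: "Cold compresses or suspension of treatment will be applied if necessary". The Combined Intervention Group section says: "If necessary, cold compresses or suspension of treatment will be applied, and the results will be recorded in the CRF". In the Spine-Pinching Group section, "skin tenderness or muscle discomfort will be monitored and recorded in the CRF", with no further action given.

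**Statistical Analysis.** The primary analysis is by intention to treat, with a per-protocol analysis as a supplement, and missing data are filled by last observation carried forward. The primary contrast is combined intervention against routine care on MoCA at week 8.

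**The concern.** Two things do not fit together.

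First, item (2) puts an ungraded word beside a graded safety scheme. A burn that pauses treatment under Safety Monitoring could be taken as grounds for removal under the withdrawal criteria, depending on how staff read *complications*.

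Second, and whatever that word means, item (2) makes removal from the study or the analysis the consequence of a safety event. Ending an intervention and ceasing to be followed or analysed are different things, and an intention-to-treat analysis depends on keeping them apart.

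The listed procedure-related events can arise only where the procedures are given, and the combined arm receives both. Removal under item (2) would therefore follow treatment assignment. Week-8 MoCA would be lost or discarded mainly on one side of the primary contrast, for a reason caused by the treatment.

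**Working it through.** **1. Item (2) against the safety tiers**

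| Event | Withdrawal item (2), *serious* governs both nouns | Withdrawal item (2), *complications* stands alone | Safety Monitoring |
|---|---|---|---|
| Mild reaction | Not covered | Covered only if it counts as a complication at all | No treatment required |
| Moderate burn | Not covered | Removed from study or analysis | Intervention paused |
| Severe event | Removed from study or analysis | Removed from study or analysis | Intervention terminated, referral |

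The middle row differs on one reading only. The bottom row differs on both: one section ends participation or analysis, the other ends the intervention. The text does not settle which reading applies.

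**2. Item (2) against the analysis**

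If the withdrawal criteria are followed, the participant may be dropped from the analysis, which is not intention to treat. If Statistical Analysis is followed, the participant stays in with a carried-forward value. The first MoCA after baseline is at week 6. Someone withdrawn before then and not seen again carries the baseline score forward, which is a change of zero. Someone withdrawn between weeks 6 and 8 carries the week-6 score. Each route can differ from the week-8 score that would have been observed.

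**3. Planned numbers**

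Sample Size Calculation: 33/(1 − 0.15) = 38.82, rounded up to 39 per group; 4 × 39 = 156. This reproduces.

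**4. Effect on power (illustration)**

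Inputs from the protocol: difference 3, SD 4, so 3/4 = 0.75 SD; α = 0.05, taken as two-sided; 39 per arm; 15% dropout, leaving 39 × 0.85 = 33.15 per arm. Assumption: a further share *r* is removed from the combined arm only, leaving 33.15 × (1 − *r*). No event rate is given, so *r* is varied.

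| *r* | Combined arm | Routine care | Two-sample t-test power |
|---|---|---|---|
| 0% | 33.15 | 33.15 | about 85% |
| 10% | 29.84 | 33.15 | about 83% |
| 20% | 26.52 | 33.15 | about 81% |
| 30% | 23.21 | 33.15 | about 78% |

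Power holds up because this two-group comparison needs about 29 per arm for 80%, fewer than the planned 33.

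**5. Effect on the estimate (illustration)**

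Suppose removed and retained participants have the same prognosis without treatment, those retained gain the planned 3 points over routine care, and those removed gain nothing over it. The difference for everyone randomised is then 3 × (1 − *r*), while an analysis that excludes the removed participants reports 3. The overstatement is 3 × *r*: 0.3 points at 10%, 0.6 at 20%, 0.9 at 30%. Carrying baseline forward could err in the other direction. The direction cannot be fixed from the documents.

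**The case against.** The strongest reply is that item (2) is a termination-level rule. Its neighbours concern poor compliance that ends treatment and severe illness that requires participation to end. Read that way, *serious* covers both nouns and the item roughly matches the severe tier. The protocol also calls redness and burns skin reactions or adverse events, never complications. This is a fair reading, and it reduces the moderate-burn conflict to an ambiguity. It is not the only reading: the neighbouring items carry their own limits and *complications* carries none.

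A second reply is that a journal article condenses the full protocol, so an undefined word is weak evidence. That stands for the definition. It does not answer the clash between removal from analysis and intention to treat, because the article states both.

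Some stronger inferences are tempting but unsupported:

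- *The plan removes anyone with any complication.* This needs the wider reading and treats every skin reaction as a complication.
- *Safety Monitoring keeps mild and paused cases on treatment.* It does not say so; this is inferred from termination being reserved for the severe tier.
- *The moxibustion and combined-arm sections set a third, conflicting rule.* They offer compresses or suspension where needed; Safety Monitoring gives a compress as an example within a pause. That is at most a small wording difference.
- *The combined arm will fall below its planned size.* No event rate is given, intention to treat with carried-forward values would keep withdrawn participants in, and the power cost is small.
- *Routine care would lose nobody.* Emotional discomfort is listed as an adverse event there, so the imbalance is a matter of degree.

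**Conclusion.** The point holds in limited form. Whether a moderate burn leads to a pause or to removal is an ambiguity, resting on one ungraded word. What holds on either reading is that item (2) ties a safety event to leaving the study or the analysis, whereas Safety Monitoring ties its severe tier to ending the intervention and the primary analysis is by intention to treat. If item (2) is followed, loss of week-8 MoCA would depend on arm and fall mainly on the combined side of the primary contrast.

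The size cannot be established from the documents. On the assumed 10% to 30% removal, power stays between about 83% and 78%. Possible bias is the larger worry: 0.3 to 0.9 points against a planned 3 in one simple scenario, proportionately less if removals are rarer. It is worth correcting because the remedy is cheap and removes an avoidable source of bias.

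**What to change.** 1. Reconcile item (2) of the withdrawal criteria with the severity tiers in Safety Monitoring and the actions in the Du-Moxibustion Group and Combined Intervention Group sections, so that one event leads to one action throughout. The investigators must state which management rule applies; this review takes no position on it.
2. Separate stopping treatment from leaving the study, and record each with its date and reason.
3. State that participants whose treatment is paused or stopped continue to be assessed, including the week-8 MoCA, unless they withdraw consent.
4. Delete exclusion from analysis as a consequence of these criteria for the intention-to-treat analysis. Any such exclusion belongs only in the supplementary per-protocol analysis.

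The cost is wording, best settled before enrolment begins. The week-8 assessment is already scheduled for every participant, so no visits are added.
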